|-------------------|------------------------------------|---------------------------------------------|----------------------------------------------|-------------------------------------------------|
|                   | Grade 1                            | Grade 2                                     | Grade 3                                      | Grade 4                                         |
| Allergic Reaction | pruritus without rash              | localized urticaria                         | generalized urticaria; angioedema            | anaphylaxis                                     |
| Headache          | mild, no treatment required        | transient, moderate; treatment required     | severe; responds to initial narcotic therapy | intractable; requires repeated narcotic therapy |
| Fever: oral       | 37.7 - 38.5 C or 100.0 - 101.5 F   | 38.6 - 39.5 C or 101.6 - 102.9 F            | 39.6 - 40.5 C or 103 - 105 F                 | > 40 C or > 105 F                               |
| Fatigue           | normal activity reduced < 48 hours | normal activity decreased 25-50% > 48 hours | normal activity decreased > 50% can't work   | unable to care for self                         |

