#### **5.2.4. Adverse events**

##### **5.2.4.1. Adverse event definition**

The following definitions will be employed for the reporting of Adverse Events:

A) Adverse Event:

An adverse event is defined as any unfavourable and unintended sign, symptom, syndrome, or illness that develops or worsens during the period of observation in the clinical study. Clinically relevant abnormal results of diagnostic procedures including abnormal laboratory findings (e.g., requiring unscheduled diagnostic procedures or treatment measures, or resulting in withdrawal from the study) which are considered by the Principal Investigator to be detrimental should be recorded as adverse events whether or not they have a causal relationship with the study drug. Where the laboratory result is a sign of another clinical condition, the clinical condition itself should be the reported adverse event. An event unequivocally caused by a significant deterioration of the underlying condition related to malaria is regarded as an adverse event.

Occurrence of *P.falciparum* infection occurring during the course of the study will be captured on a specific form on the CRF. However these events will not be reported as adverse events unless the resulting malaria is of an unexpected severity.

B) Unexpected Adverse Event:

Any adverse experience that has not been previously observed (i.e. included in the protocol or Investigator's Brochure) whether or not the event is anticipated because of the pharmacologic properties of the study drug.

C) Serious Adverse Event

Any adverse experience occurring at any dose that results in any of the following outcomes:

- **Death.**
- **Life threatening-** defined as an experience that places the patient or subject, in the view of the Investigator, at immediate risk of death from the reaction as it occurred. (Note: this does not include a reaction that, had it occurred in a more severe form, might have caused death).
- Requires inpatient **hospitalisation** or prolongation of existing hospitalisation.
- Results in a **congenital** anomaly or birth defect.
- Results in a **persistent or significant disability** or incapacity.

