#### 5.2.4.2. Assessment of adverse events

A) Severity

The Investigator will assess the severity/intensity of the adverse reactions and clinical laboratory changes using the DMID Toxicity Grading Scale for Determining the Severity of Adverse Events provided in Protocol Attachment 7.

If an adverse event is not listed in the DMID table, the Investigator will assess the severity using the following guidelines:

1 = Mild: awareness of sign or symptom, but easily tolerated

2 = Moderate: enough discomfort to cause interference with usual activity

- 3 = Severe: incapacitating with inability to work or do usual activity  
4 = Life-Threatening

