**Clarification of the difference in meaning between “severe” and “serious”**

The term “severe” is often used to describe the intensity (severity) of a specific event (as in mild, moderate, or severe myocardial infarction); the event itself, however, may be of relatively minor medical significance (such as severe headache). This is not the same as “serious”, which is based on the outcome or criteria defined under the serious adverse event definition. An event can be considered serious without being severe if it conforms to the seriousness criteria, similarly severe events that do not conform to the criteria are not necessarily serious. Seriousness (not severity) serves as a guide for defining regulatory reporting obligations.

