**Adverse Events**

Adverse events (AEs) will be summarized by presenting, for each treatment

group, the number and percentage of patients having any AE, having an AE in each system organ class and having each individual AE (preferred term). Additionally, a summary of adverse events by preferred term and severity will be performed using the worst severity grade.

All related AEs, AEs with outcome death, AEs leading to permanent discontinuation of treatment, SAEs and related SAEs will be summarized by percentages and frequencies and listed including the Investigator term, the preferred term, start and end date of AE, duration (days), severity, drug relationship, action taken and outcome.

Treatment related AEs are those rated by the Investigator as “definite”, “probable”, “possible”. In case relationship is unknown or missing the worst case will be assumed and the AE will be considered to be drug related.

Adverse events will be coded using the latest available MedDRA dictionary version.

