#### **ESTIMATING SEVERITY GRADE**

For abnormalities NOT found elsewhere in the Toxicity Tables use the scale below to estimate grade of severity:

**GRADE 1 Mild** Transient or mild discomfort

(< 48 hours); no medical intervention/therapy required

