#### **SERIOUS OR LIFE-THREATENING AEs**

ANY clinical event deemed by the clinician to be serious or life-threatening should be considered a grade 4 event. Clinical events considered to be serious or life-threatening include, but are not limited to: seizures, coma, tetany, diabetic ketoacidosis, disseminated intravascular coagulation, diffuse petechiae, paralysis, acute psychosis, severe depression.

| HEMATOLOGY                           |                                                 |                                           |                                   |                                                                            |
|---------------------------------------------|-------------------------------------------------|-------------------------------------------|-----------------------------------|----------------------------------------------------------------------------|
|                                             | Grade 1                                         | Grade 2                                   | Grade 3                           | Grade 4                                                                    |
| Haemoglobin                                 | 9.5 - 10.5 gm/dL                                | 8.0 - 9.4gm/dL                            | 6.5 - 7.9 gm/dL                   | < 6.5 gm/dL                                                                |
| Absolute Neutrophil Count                   | 1000-1500/mm                        | 750-999/mm                    | 500-749/mm            | <500/mm                                                        |
| Platelets                                   | 75,000-
99,999/mm                | 50,000-
74,999/mm          | 20,000-
49,999/mm  | <20,000/mm                                                     |
| WBCs                                        | > 13,000/ mm                        | 13,000-
15,000 /mm         | 15,000-
30,000/mm  | >30,000 or <1,000
/mm                                       |
| % Polymorphonuclear Leucocytes + Band Cells | > 80%                                           | 90 – 95%                                  | >95%                              | -----                                                                      |

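### Attachment 7 ties seriousness to Grade 4 against section 5.2.4.2, and some adult bands overlap, so one adverse event can carry two severity grades

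*Protocol*

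**What the plan says.** Section 5.2.4.2 has the investigator grade the severity of adverse reactions and "clinical laboratory changes using the DMID Toxicity Grading Scale for Determining the Severity of Adverse Events provided in Protocol Attachment 7". Section 5.2.2 repeats this for laboratory values outside the reference range. Events that the scale does not list go to a four-level scale in section 5.2.4.2 itself: "If an adverse event is not listed in the DMID table, the Investigator will assess the severity using the following guidelines".

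The clarification in section 5.2.4.2 then separates the two concepts: "An event can be considered serious without being severe if it conforms to the seriousness criteria". Seriousness is defined in section 5.2.4.1 by outcome, and one criterion is "inpatient hospitalisation or prolongation of existing hospitalisation".

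Attachment 7, under its heading on serious or life-threatening events in the adult tables, says "ANY clinical event deemed by the clinician to be serious or life-threatening should be considered a grade 4 event".

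The grades are used in section 9.5.2 (Adverse Events), where "a summary of adverse events by preferred term and severity will be performed using the worst severity grade".

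**The concern.** An investigator who follows section 5.2.4.2 and one who follows the Attachment 7 sentence can give the same adult event different grades. For some white cell counts, alkaline phosphatase values and temperatures the printed bands also admit more than one grade. For adolescents the grade depends on which table the site chooses.

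Safety is part of the primary objective, and the worst-severity summary is a planned safety output. A Grade 4 entry reads as life-threatening. If some entries only reflect an admission or an overlapping band, the table overstates severity. For clinical events this cannot be repaired at analysis, because the investigator has already recorded the grade under conflicting instructions.

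**Working it through.** The plan states no figure to reproduce here. The check sets the passages side by side and reads test values against the printed bands.

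**1. Seriousness and grade**

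Take an adult with generalised urticaria who is admitted for treatment.
- Attachment 7, adult allergic reaction row: Grade 3 (Grade 4 is anaphylaxis).
- Section 5.2.4.1: serious, because of the admission.
- Section 5.2.4.2 clarification: seriousness does not change severity, so Grade 3 stands.
- Attachment 7 sentence, if serious has its section 5.2.4.1 meaning: Grade 4.

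Attachment 7 is also inconsistent with itself. Its general Grade 3 allows for possible hospitalisation, and the adult hypokalaemia and hypophosphataemia rows put required hospitalisation at Grade 3. Several other adult rows (nausea, vomiting, diarrhoea, hypertension) already put required hospitalisation at Grade 4, so the conflict does not touch admissions for those events.

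**2. Overlapping adult bands for variables the trial measures**

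White cells and alkaline phosphatase are in Table 1; temperature is measured throughout.

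| Adult row | Printed bands | Test value | Grades met |
|---|---|---|---|
| WBC, /mm3 | G1 >13,000; G2 13,000-15,000; G3 15,000-30,000; G4 >30,000 or <1,000 | 14,000 | 1, 2 |
| | | 15,000 | 1, 2, 3 |
| | | 20,000 | 1, 3 |
| | | 35,000 | 1, 4 |
| Alkaline phosphatase, x ULN | G1 1.25-2.5; G2 1.6-5 | 2.0 | 1, 2 |
| Oral fever, C | G3 39.6-40.5; G4 >40 | 40.2 | 3, 4 |

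Share of the alkaline phosphatase Grade 1 band that is also Grade 2: (2.5 - 1.6) / (2.5 - 1.25) = 0.9 / 1.25 = 0.72.

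Fever Grade 3 is printed as "39.6 - 40.5 C or 103 - 105 F". The two Grade 4 limits are not equivalent: 40 C = 40 x 1.8 + 32 = 104 F, while 105 F = (105 - 32) / 1.8 = 40.6 C. The Fahrenheit bands do not overlap; the Celsius bands do.

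The worst-grade rule in section 9.5.2 does not settle these cases. As I read it, it selects among grades already recorded and does not tell an investigator which of two matching bands to record.

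**3. Adult and paediatric tables**

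Patients are aged 3 to 60. The protocol gives no age at which the adult table takes over. The paediatric creatinine row has a category above 12 years with no upper limit. The tables disagree:
- AST or ALT at 6 x ULN: adult Grade 3 (5.1-10), paediatric Grade 2 (5.0-9.9).
- Haemoglobin 7.5 g/dL: adult Grade 3 (6.5-7.9), paediatric Grade 2 (7.0-9.9).

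**The case against.** The best defence is that Attachment 7 uses serious to mean clinically grave. Its examples include seizures, coma and paralysis, and its Grade 3 entries show that admitted patients were expected below Grade 4. On that reading one word has two senses and nothing is regraded. This is plausible, and it is why the point is minor. But the attachment does not say so, and the only definition in the protocol is by outcome criteria, so an investigator has no textual basis for the narrower sense.

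A reader might infer more than the documents support:
- **That Attachment 7 grades every adverse event.** Section 5.2.4.2 has its own scale for unlisted events. Attachment 7 offers a second, differently worded one ("For abnormalities NOT found elsewhere in the Toxicity Tables use the scale below to estimate grade of severity"), a lesser inconsistency.
- **That a precautionary stay becomes Grade 4.** Section 5.2.4.1 excludes observation of high-risk patients from serious events. The conflict needs an admission for treatment.
- **That the rule covers children.** It stands under the adult tables and is not repeated in the paediatric ones.
- **That the number of misgraded events can be projected from phase II.** That study was in falciparum malaria, at ages 15 to 60, with all dose groups on pyronaridine artesunate. Its 6 serious events occurred in 4 patients, while the planned summary counts patients.
- **That one arm is favoured.** Grading is double-blind and complete randomisation blocks go to each site, so site-dependent grading gives no evident advantage to either arm.
- **That the laboratory summaries are affected.** Section 9.5.2 bases them on clinical significance, normal-range shifts and descriptive statistics, not toxicity grades. The white cell and alkaline phosphatase overlaps reach that section's outputs only through values reported as adverse events.
- **That six vomiting episodes certainly have no adult grade.** The print gives 2-5 and then >6. Other rows, such as methaemoglobin, show a similar gap at the boundary, so a lost greater-than-or-equal sign is possible.

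**Conclusion.** The attachment is wrong as written, and the defect is minor. Read literally, the Grade 4 sentence contradicts section 5.2.4.2 and other entries of Attachment 7. Three adult bands for measured variables overlap, and the age boundary between two disagreeing tables is not stated.

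The consequence is misclassified adverse event severity and possibly inflated Grade 4 counts in the worst-severity summary. The protocol does not allow the number of affected patients to be estimated. It depends on how many adults have events that are serious only through admission for treatment, how many reported events fall in the overlapping bands, and which table sites use for adolescents. Serious events are also listed individually with severity, action and outcome, so an inflated grade on one of them could be seen there. The Day 14 cure analysis and the sample size are unaffected.

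The conclusion assumes that the bands were reproduced correctly from the protocol file. For vomiting that is uncertain, so it is only a point to check.

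**What to change.** 1. Reconcile the Attachment 7 sentence with section 5.2.4.2 so that seriousness alone does not set the grade.
2. Make the adult bands for white cells, alkaline phosphatase and Celsius fever mutually exclusive, taking the limits from the source scale. Check the vomiting boundary at 6 episodes against the same source.
3. State the age at which the paediatric table applies.

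The cost is a correction to one attachment and a short notice to sites. Deriving laboratory grades centrally from the recorded values would remove site choice for those variables. It is optional, since the planned laboratory summaries use no grades.

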#### Choice of comparator

In spite of the increasing numbers of resistant strains, chloroquine monotherapy is still recommended as standard blood-stage therapy for patients with *P. vivax* malaria in the countries in which this trial will be conducted. Its selection as comparator is therefore justified. The adult dose of chloroquine will be 620 mg for 2 days followed by 310 mg on the third day and for children 10 mg/kg for the first two days and 5 mg/kg for the third day. Total dose is in accordance with the current practice in the countries where the study is conducted. The safety profile of chloroquine is well established and known. Although generally well tolerated, the following side-effects of chloroquine treatment have been described:

Gastro-intestinal disturbances, headache, hypotension, convulsions, visual disturbances, depigmentation or loss of hair, skin reactions (rashes, pruritus) and, rarely, bone-marrow suppression and hypersensitivity reactions such as urticaria and angioedema. Their occurrence during the present trial may however be unlikely given the short (3-day) duration of treatment.

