|                        | Grade 1                          | Grade 2                                        | Grade 3                                          | Grade 4                                                                                                                                 |
| Mucocutaneous          | erythaema; pruritus              | diffuse, maculo papular rash, dry desquamation | vesiculation or moist desquamation or ulceration | exfoliative dermatitis, mucous membrane involvement or erythaema, multiforme or suspected Stevens-Johnson or necrosis requiring surgery |
| Induration             | < 15mm                           | 15-30 mm                                       | >30mm                                            |                                                                                                                                         |
| Erythaema              | < 15mm                           | 15-30 mm                                       | >30mm                                            |                                                                                                                                         |
| Oedema                 | < 15mm                           | 15-30 mm                                       | >30mm                                            |                                                                                                                                         |
| Rash at Injection Site | < 15mm                           | 15-30 mm                                       | >30mm                                            |                                                                                                                                         |
| Pruritus               | slight itching at injection site | moderate itching at injection extremity        | itching over entire body                         |                                                                                                                                         |

| SYSTEMIC          |                                    |                                             |                                              |                                                 |

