## PEDIATRIC TOXICITY TABLES

| LOCAL REACTIONS        |                                  |                                         |                                                |                          |
|------------------------|----------------------------------|-----------------------------------------|------------------------------------------------|--------------------------|
|                        | GRADE 1                          | GRADE 2                                 | GRADE 3                                        | GRADE 4                  |
| Induration             | < 10mm                           | 10-25 mm                                | 26-50mm                                        | >50mm                    |
| Erythaema              | < 10mm                           | 10-25 mm                                | 26-50mm                                        | >50mm                    |
| Oedema                 | < 10mm                           | 10-25 mm                                | 26-50mm                                        | >50mm                    |
| Rash at Injection Site | < 10mm                           | 10-25 mm                                | 26-50mm                                        | >50mm                    |
| Pruritus               | Slight itching at injection site | Moderate itching at injection extremity | Itching at injection extremity and other sites | Itching over entire body |

| HEMATOLOGY                                           |                          |                               |                               |                                      |
|------------------------------------------------------|--------------------------|-------------------------------|-------------------------------|--------------------------------------|
|                                                      | GRADE 1                  | GRADE 2                       | GRADE 3                       | GRADE 4                              |
| Haemoglobin for children greater than 2 years of age | 10-10.9 gm/dL            | 7.0-9.9 gm/dL                 | <7.0 gm/dL                    | Cardiac Failure secondary to anaemia |
| Absolute Neutrophil Count                            | 750-1200/mm  | 400-749/mm        | 250-399/mm        | <250/mm                  |

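### Attachment 7 grades the same mild whole-body itch 1 or 3 in adults and 1 or 4 in children, with no rule for choosing between rows

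*Protocol*

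**What the plan says.** Section 5.2.4.2 of the protocol makes the DMID tables in Attachment 7 the severity instrument. The four-step intensity scale printed in that section (tolerated, interfering with usual activity, incapacitating, life-threatening) is for events that the tables do not list. Attachment 7 has a general scale of its own, with the same restriction.

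Pruritus is listed in five rows. In the adult Skin table, the Pruritus row gives Grades 1 and 2 as "slight itching at injection site | moderate itching at injection extremity" and Grade 3 as "itching over entire body"; its Grade 4 cell is empty. In the paediatric Local Reactions table, "Itching over entire body" is Grade 4. The adult Mucocutaneous row has pruritus at Grade 1. The adult Allergic Reaction row has "pruritus without rash" at Grade 1, and the paediatric Allergy row does the same.

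Section 1 (Choice of comparator) names "skin reactions (rashes, pruritus) and, rarely, bone-marrow suppression" among the known effects of chloroquine, and then adds: "Their occurrence during the present trial may however be unlikely given the short (3-day) duration of treatment". Section 9.5.2 (Adverse Events) plans, by treatment group, "a summary of adverse events by preferred term and severity will be performed using the worst severity grade". Section 2 makes safety part of the primary objective.

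**The concern.** Both study treatments, and the primaquine given from Day 28, are taken by mouth. The Pruritus rows describe itch at and around an injection, so their lower grades cannot describe drug-related itch in this trial. What remains is a top grade set by body area, with no reference to intensity or function. An investigator who looks up the event by its name reaches that row. One who judges that an injection-site row cannot apply reaches a Grade 1 row. Both are following the protocol.

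The grade goes into a table that compares the arms. If generalised itch is commoner on chloroquine, the name-matched row turns a difference in mild itch into a difference in events graded severe or above. Blinding does not prevent this: misgrading applied equally in both arms still produces a difference when the misgraded event is more frequent in one of them.

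**Working it through.** The protocol states no figure that this point could reproduce. The check is a comparison of rows, followed by an illustration.

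**Step 1. One patient, several grades.** Take whole-body itch that is easily tolerated, with no rash.

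| Patient | Row in Attachment 7 | Grade |
|---|---|---|
| Adult | Skin, Pruritus | 3 |
| Adult | Skin, Mucocutaneous | 1 |
| Adult | Systemic, Allergic Reaction | 1 |
| Child | Local Reactions, Pruritus | 4 |
| Child | Other, Allergy | 1 |

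The spread is 3 − 1 = 2 grades in adults and 4 − 1 = 3 grades in children. The intensity scale in section 5.2.4.2 would call this itch mild, but it may be used only for an unlisted event.

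**Step 2. Is there a precedence rule?** Neither section 5.2.4.2 nor Attachment 7 says which row wins when several name the same symptom. Neither says that the injection-site rows are to be ignored for oral drugs.

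**Step 3. What it could do to the by-arm table.** The only input from the documents is 228 randomised patients per arm (section 9.4). Pruritus rates and the share of itch that is whole-body are assumptions, because the protocol gives neither. If every such case is graded on the Pruritus row:

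expected Grade 3–4 itch events = 228 × pruritus rate × whole-body share

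With a whole-body share of one half:

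| Assumed rate, chloroquine v pyronaridine artesunate | Chloroquine | Pyronaridine artesunate | Excess on chloroquine |
|---|---|---|---|
| 1% v 1% | 228 × 0.01 × 0.5 = 1.1 | 1.1 | 0 |
| 5% v 1% | 228 × 0.05 × 0.5 = 5.7 | 1.1 | 4.6 |
| 10% v 2% | 228 × 0.10 × 0.5 = 11.4 | 2.3 | 9.1 |
| 20% v 2% | 228 × 0.20 × 0.5 = 22.8 | 2.3 | 20.5 |

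The counts scale in proportion to the share. At 20% v 2%, a share of one quarter gives 11.4 v 1.1, and a share of one gives 45.6 v 4.6. If the Grade 1 rows are used instead, mild itch adds no Grade 3–4 event in either arm on any line.

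The illustration shows that the result depends on the row chosen and on rates nobody has stated. It is not an estimate.

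**The case against.** The strongest reply is that the tables do not force a high grade. The paediatric Pruritus row stands under a heading for local reactions, and the adult row follows others about injection sites, so a sensible investigator giving tablets would pass over them and use a Grade 1 row. This stands in part. A reader might infer that itching is always graded by the injection-site row and that severe events on chloroquine are therefore inflated. The documents do not support that, because three rows offer Grade 1. But nothing directs the investigator to those rows, and the row bearing the event's name is the one that gives Grade 3 or 4.

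Second, the protocol itself thinks chloroquine's listed effects may be unlikely with three days of treatment, and exclusion criteria 5 and 6 remove patients with known reactions to it. Not naming pruritus for the combination is no evidence that it is rare there. This stands: a between-arm excess cannot be asserted, and zero is within the range.

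Third, the worst-grade table is descriptive and by preferred term, so severe itch would be visible on its own line, and no test or stopping rule in the protocol uses it. This also stands. It limits the harm but does not make the grades correct.

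Fourth, a reader might infer that serious-event counts would shift, because section 5.2.4.1 gives a deterioration in toxicity grade as an example of a ground for seriousness. That example is permissive and rests on medical judgement that the patient is in jeopardy, and section 5.2.4.2 separates severity from seriousness. Mild itch does not become serious through a table cell.

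**Conclusion.** The point holds as an internal contradiction in the grading rule. The same mild generalised itch without rash may be Grade 1 or 3 in an adult and Grade 1 or 4 in a child, no precedence is stated, and the scale that would settle it is closed because pruritus is listed. The grade feeds a by-arm safety table in a trial whose primary objective includes safety.

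The likely direction, if there is one, is against chloroquine, since pruritus is named for it. The size is unknown. It depends on how many investigators use the Pruritus row, on how often generalised itch occurs in each arm, and on whether those rates differ. With a half share of whole-body itch, the assumed rates above give anything from no excess to about 20 events. The primary efficacy analysis is not touched, and no effect on serious-event counts is shown. This is more than missing detail, because the conflicting grades are written into the protocol. It should be corrected, but it does not threaten the trial's main conclusion.

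**What to change.** Before grading starts, state in Attachment 7 and in section 5.2.4.2 that:

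- the injection-site and local-reaction rows, including Pruritus, do not apply to oral study drug;
- pruritus without other skin or allergic signs is graded, in adults and children alike, by the intensity scale in section 5.2.4.2;
- this is an explicit exception both to the condition that the scale is only for unlisted events and to the Grade 1 pruritus entries in the adult Mucocutaneous, adult Allergic Reaction and paediatric Allergy rows.

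The third item is needed because removing the injection-site rows alone would leave pruritus listed at Grade 1 and the intensity scale still closed to it. Timing matters: the protocol does not ask sites to record which row was used, so a grade alone would not later show how it was reached.

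The cost is a few sentences in the protocol, repeated in the CRF guide. There is no new procedure, data item or change in sample size. The downside is that fewer itch events will be reported as severe, so the comparator may look slightly better.
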